# Improving sexual health in men with prostate cancer: randomised controlled trial of exercise and psychosexual therapies

**DOI:** 10.1186/1471-2407-14-199

**Published:** 2014-03-18

**Keywords:** Prostate cancer, Sexual health, Erectile dysfunction, Exercise, Resistance training, Aerobic exercise, Psychosexual support, Self-management

## Abstract

**Background:**

Despite being a critical survivorship care issue, there is a clear gap in current knowledge of the optimal treatment of sexual dysfunction in men with prostate cancer. There is sound theoretical rationale and emerging evidence that exercise may be an innovative therapy to counteract sexual dysfunction in men with prostate cancer. Furthermore, despite the multidimensional aetiology of sexual dysfunction, there is a paucity of research investigating the efficacy of integrated treatment models. Therefore, the purpose of this study is to: 1) examine the efficacy of exercise as a therapy to aid in the management of sexual dysfunction in men with prostate cancer; 2) determine if combining exercise and brief psychosexual intervention results in more pronounced improvements in sexual health; and 3) assess if any benefit of exercise and psychosexual intervention on sexual dysfunction is sustained long term.

**Methods/Design:**

A three-arm, multi-site randomised controlled trial involving 240 prostate cancer survivors will be implemented. Participants will be randomised to: 1) ‘Exercise’ intervention; 2) ‘Exercise + Psychosexual’ intervention; or 3) ‘Usual Care’. The Exercise group will receive a 6-month, group based, supervised resistance and aerobic exercise intervention. The Exercise + Psychosexual group will receive the same exercise intervention plus a brief psychosexual self-management intervention that addresses psychological and sexual well-being. The Usual Care group will maintain standard care for 6 months. Measurements for primary and secondary endpoints will take place at baseline, 6 months (post-intervention) and 1 year follow-up. The primary endpoint is sexual health and secondary endpoints include key factors associated with sexual health in men with prostate cancer.

**Discussion:**

Sexual dysfunction is one of the most prevalent and distressing consequences of prostate cancer. Despite this, very little is known about the management of sexual dysfunction and current health care services do not adequately meet sexual health needs of survivors. This project will examine the potential role of exercise in the management of sexual dysfunction and evaluate a potential best-practice management approach by integrating pharmacological, physiological and psychological treatment modalities to address the complex and multifaceted aetiology of sexual dysfunction following cancer.

**Trial registration:**

Australian New Zealand Clinical Trials Registry ACTRN12613001179729.

## Background

Increasing prostate cancer incidence (~56% increase since 1991) and survival rates (5-year survival rate increased from ~58% to ~92% since 1987) coupled with an aging population have led to a large and rapidly growing population with unique health care requirements [1]. Sexual dysfunction is one of the most common, distressing and persistent adverse effects of prostate cancer treatments [2-11] which has a profound impact on quality of life both for the patient and his partner [2-4,10,12-14]. The level of concern associated with sexual dysfunction is reflected by the willingness of men to sacrifice survival for sexual potency (i.e. 68% of men are willing to sacrifice a ~10% greater advantage in 5-year survival to maintain sexual function) [15]. Up to 90% of men will experience sexual dysfunction following primary therapy for prostate cancer with treatments frequently leading to erectile dysfunction, loss of libido, penile shortening and altered orgasmic experience [2-11]. Current health care services are inadequate to address the demand for management of sexual dysfunction [3], with 47% of prostate cancer survivors reporting unmet sexual health care needs [16]. Management strategies predominately involve pharmacological interventions to address the direct physiological effects of prostate cancer treatment on erectile function [17,18]. However, the aetiology of sexual dysfunction is multifaceted and there are considerable physiological and psychological side effects of prostate cancer treatments which contribute to sexual dysfunction that are not counteracted by pharmacological intervention [3,4,10]. Exercise has established efficacy for improving many of these factors in prostate cancer patients including changes in body composition (especially to counteract body feminisation with androgen deprivation therapy [ADT]), fatigue, physical function, risk of co-morbid conditions, inflammatory state, depression, anxiety and quality of life [19-25]. Emerging data indicates that exercise also fosters improved feelings of masculinity and has a positive impact on libido in men with prostate cancer [26,27], a concern that is highly prevalent and difficult to treat [3,12]. Furthermore, psychological therapies have established efficacy for improving treatment induced psychological changes associated with prostate cancer including depression and anxiety as well as enhanced quality of life [28-31] with emerging evidence for improving sexual health in prostate cancer patients [32,33]. Therefore, a multidisciplinary management strategy incorporating pharmacological (usual medical care), physiological (exercise program) and psychological (brief psychosexual self-management) interventions may represent a best-practice model for addressing sexual dysfunction secondary to prostate cancer treatment [27]. The relatively low uptake, compliance and satisfaction with current treatment options [34-36] coupled with the low help-seeking and health service utilisation behavior of men [37-39] provides additional rationale for the novel management approach proposed. Hence, the aims of this study are to:

1. Examine the efficacy of exercise as a therapy to aid in the management of sexual dysfunction in men with prostate cancer.

2. Determine if combining exercise and brief psychosexual self-management results in more pronounced improvements in the sexual health of men with prostate cancer.

3. Assess if any benefit of exercise and brief psychosexual self-management on sexual dysfunction in men with prostate cancer is sustained long term.

We will evaluate three main hypotheses: 1) Compared with usual medical care, exercise will improve sexual health in men with prostate cancer who are concerned by sexual dysfunction. We theorise that exercise will improve masculine self-esteem, quality of life, psychological distress, fatigue, body composition, body image and physical function, culminating in increased sexual health; 2) When exercise and brief psychosexual self-management are combined, improvements in sexual health will exceed those observed in usual medical care and exercise therapy alone. We theorise that brief psychosexual self-management will further enhance improvements in sexual health through increasing men’s ability to better self-manage their well-being and sexual dysfunction (i.e. enhanced uptake of pharmacologic management of erectile dysfunction); and 3) Improvements in sexual health will be sustained 1 year after completion of the exercise and combined exercise and psychosexual interventions. We hypothesise that the theoretically based interventions will prompt behavioural change that leads to sustained improvements in sexual health.

Despite being a critical survivorship care issue, there is a clear gap in current knowledge of the optimal treatment of sexual dysfunction in men with prostate cancer. The current study will generate information to address this gap. There is a strong theoretical rationale [27] and emerging evidence [26] that exercise is an innovative therapy to counteract sexual dysfunction in men with prostate cancer. However, there is a distinct lack of research investigating the efficacy of exercise on sexual health following cancer treatment. Furthermore, despite the multidimensional aetiology of sexual dysfunction, there is a paucity of research investigating the efficacy of integrated treatment models. This study will address these limitations. Findings will expand current clinical guidelines for the management of sexual dysfunction in men with prostate cancer and, importantly, facilitate the development of targeted supportive care services for survivors concerned by their sexual health. Evidence gained may lead to a paradigm shift in the management of sexual dysfunction in prostate cancer survivors.

## Methods/Design

A single-blinded (investigators blinded to group allocation), three arm, multi-site randomised controlled trial (RCT) design will be used to examine the efficacy of exercise and psychosexual therapies on sexual health in men with prostate cancer. An ‘Exercise’ group will complete the exercise intervention, an ‘Exercise + Psychosexual’ group will complete the same exercise intervention as well as a brief psychosexual self-management intervention and a ‘Usual Care’ group will maintain usual medical care for a period of 6 months. The Usual Care group will be offered participation in the interventions at the completion of the 6-month period (half to receive the Exercise intervention and half the Exercise + Psychosexual intervention). The RCT will be followed by a prospective cohort study examining the long-term impact of exercise versus exercise and brief psychosexual self-management on sexual dysfunction in prostate cancer patients 1 year after the interventions (Figure 1). The study will be guided by the CONSORT statement [40].

**Figure 1 F1:**
[figure not shown]
**Summary of the study design.** Self-report measures also assessed at 6 months follow-up (i.e. at 12 months for both the Exercise and the Exercise + Psychosexual groups; 18 months for the usual care group).

### Participants

Two hundred and forty men (80 subjects per arm) treated for prostate cancer will be recruited by invitation from their attending specialist (oncologist/urologist). Participants will be recruited in Perth, Western Australia; Brisbane, Queensland; Central and North Coasts of New South Wales. Inclusion criteria are: 1) concern about sexual health as assessed by an International Index of Erectile Functioning (IIEF) overall satisfaction score < 8 (i.e. moderately-very dissatisfied) [41] and/or Expanded Prostate Cancer Index Composite (EPIC) sexual bother score > 8 (i.e. small-big problem) [42]; 2) prior/current treatment for prostate cancer including prostatectomy, radiotherapy or ADT; and 3) physician consent. Exclusion criteria are: 1) non-nerve sparing prostatectomy; 2) > 6 months since prostatectomy or completion of radiotherapy or ADT; 3) incontinence defined as requiring the use of > 1 pad in a 24-hour period; 4) already performing regular exercise defined as undertaking structured aerobic or resistance training two or more times per week within the past 3 months; 5) acute illness or any musculoskeletal, cardiovascular or neurological disorder that could inhibit exercise or put participants at risk from exercising; and 6) unable to read and speak English. Eligible subjects will undertake a series of familiarisation sessions and baseline measurements prior to randomisation (Figure 2). The protocol has been approved (ID: 10643 [name]) for all participating centres by the Edith Cowan University Human Research Ethics Committee and all participants will provide written informed consent.

**Figure 2 F2:**
[figure not shown]
CONSORT diagram depicting the flow of participants throughout the trial.

### Randomisation

Subjects will be randomly allocated in a ratio of 1:1:1 to the three study arms, subject to maintaining approximate balance regarding stratification for: 1) age (<60 years≥); 2) current sexual activity level (no/minor-moderate) as assessed by the European Organisation for Research and Treatment of Cancer (EORTC) prostate cancer specific questionnaire (QLQ-PR25) sexual activity score [43]; 3) previous prostatectomy (yes/no); 4) previous radiotherapy (yes/no); and 5) previous/current ADT (yes/no). A research methods consultant with no patient contact will be responsible for randomisation which will be performed in Statistical Analysis System using the Pocock-Simon minimisation algorithm.

The inclusion and exclusion criteria and stratification procedures have been designed to control for the major factors that may influence either baseline values and/or the potential for change in sexual health throughout the intervention (e.g. treatment type, time since treatment, level of sexual health both pre-treatment and at baseline, age, potential for recovery of function, incontinence). Furthermore, in addition to clinically relevant covariates, the main factors that could potentially confound the results will be assessed and adjusted for (e.g. utilisation of sexual aids [pre-treatment, post-treatment and throughout the study period], relationship status and satisfaction, any additional cancer treatment during the study period, side effects and co-morbidities influencing sexual health).

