### Measurements

All measurements for primary and secondary endpoints will take place at baseline, post-intervention and 1 year follow-up. The Usual Care group will undergo an additional assessment point at the end of their delayed intervention. All groups will complete an additional assessment at 6 months follow-up involving the self-report questionnaires only. All assessments tools and procedures have established validity and reliability and are used widely in clinical research.

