### Secondary study endpoints

Secondary endpoints include key factors associated with sexual health in men with prostate cancer.

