#### Relationship satisfaction

The Dyadic Adjustment Scale will assess relationship satisfaction between participants and their partners [49].

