
#### Exercise and psychosexual intervention

Participants receiving the combined exercise and psychosexual support and self-management will complete the exercise intervention described above as well as a brief psychosexual self-management component that addresses psychological and sexual well-being. A low intensity psychological care approach will be utilised in order to maximise uptake and accessibility (i.e. facilitates translation) [62]. Specifically, at baseline, participants will receive a face to face brief psychosexual self-management session with their exercise physiologist that addresses: stress management; problem solving coping for treatment challenges; and goal setting for sexual rehabilitation. These sessions will be audiotaped with 15% reviewed to ensure adherence to the intervention protocol. The psychosexual self-management intervention will apply cognitive behavioural strategies; will utilise an adult learning approach in which men self-select goals to focus on; and will encourage self-management [63]. To support self-management men will receive a psychosexual kit that includes a published self-help book for men with prostate cancer and their partners [64]; study specific tip sheets about treatments for erectile dysfunction and goal setting for sexual rehabilitation; a progress journal-diary; and audio resources for stress management. The intervention delivered by the exercise physiologist will be manualised and based on existing materials already developed and trialled by the team [31,48]. The exercise physiologists will receive extensive training in how to deliver the intervention and continued supervision. Treatment fidelity will be managed consistent with National Institute of Health guidelines [65]. This pragmatic approach has been adopted based on the fact that men are low help-seekers and incorporating strategies that are linked to masculine ideals (i.e. exercising linked to physical strength, self-management as self-reliance, peer support offered through exercising in a group or ‘team’ of men rather than a traditional support group setting) may be more accepted by men and effective [37-39].

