#### Statistical analysis

Data from our previous 3-month study in prostate cancer patients indicates that the standard deviation for change in our primary outcome of sexual health equates to ~22 points on the QLQ-PR25 sexual activity domain [26]. We observed the mean change after the intervention to differ between exercise and usual care groups by ~11 points [26]. There is no available evidence comparing changes in sexual health between exercise and psychosexual interventions. However, data from previous psychosexual interventions in prostate cancer patients indicates changes of a moderate standardised effect (*d* = 0.5) in sexual health following the psycho-educational interventions [32,33]. We have based sample size calculations on the assumption that there will be an additive effect of exercise and psychosexual therapies. A priori, 64 participants per group will be required to achieve 80% power at an alpha level of 0.05 (two tailed), and to demonstrate a difference between the three groups in sexual health at the end of the intervention. Previous experience in exercise and psychosexual therapy trials indicates an attrition rate of up to 20% over the intervention period. Therefore, to adequately ensure that we have sufficient participant numbers at the end of the intervention, 240 participants will be randomised to the study arms. A sample size of 240 will also provide us with sufficient power to detect a moderate standardised effect (*d* = 0.5) in our secondary outcomes. Based on previous experience we anticipate a further attrition rate of up to 20% over the follow-up period. Therefore, the sample size will provide 87% statistical power to detect differences between the Exercise group and the Exercise + Psychosexual group at follow-up (*d* = 0.5; n = 77 per group as the usual care group will be split between the two interventions for the prospective cohort study component of this project).

Data will be analysed using an intention-to-treat approach with maximum likelihood imputation of missing values. Analyses will include standard descriptive statistics, Student’s t-tests, chi-square, correlation and regression, and two way (group × time) repeated measures ANOVA (or ANCOVA as appropriate) to examine differences between groups over time. Clinically relevant covariates will be included in analyses. All tests will be two-tailed and an alpha level of 0.05 will be applied as the criterion for statistical significance.

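### The plan adjusts for sexual-aid use during the study, which its own hypothesis makes a route of the psychosexual effect, so the adjustment removes part of the effect under test

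*Protocol article*

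**What the plan says.** The Randomisation section of the protocol article states that "the main factors that could potentially confound the results will be assessed and adjusted for". Its examples begin with aid use at three times, the last being the study itself: "adjusted for (e.g. utilisation of sexual aids [pre-treatment, post-treatment and throughout the study period], relationship status and satisfaction". The list continues with cancer treatment added while the study runs, and with side effects and co-morbidities that bear on sexual health. Only the sexual-aid item and the added-treatment item carry an on-study timing.

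The Statistical analysis section commits to intention-to-treat and to group-by-time repeated measures ANOVA or ANCOVA. It adds: "Clinically relevant covariates will be included in analyses". It does not restrict these to baseline values.

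Three other places give on-study aid use a different role:

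- **Background, hypothesis 2.** The psychosexual component is expected to help men manage their well-being and dysfunction themselves, glossed as "i.e. enhanced uptake of pharmacologic management of erectile dysfunction".
- **Exercise and psychosexual intervention.** The kit contains "study specific tip sheets about treatments for erectile dysfunction and goal setting for sexual rehabilitation".
- **Secondary study endpoints.** Utilisation of sexual aids has its own heading in this group, which is introduced with "Secondary endpoints include key factors associated with sexual health in men with prostate cancer".

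**The concern.** A confounder of a treatment comparison is a common cause of treatment and outcome. Here treatment is set by randomisation, so nothing that happens afterwards can be a cause of it. On-study aid use and added cancer treatment can only be consequences of allocation or unrelated to it, and neither case calls for adjustment to remove confounding.

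For aid use the protocol goes further. It says that the psychosexual component should raise it, supplies material to that end, and measures it as an outcome. A model that holds aid use constant compares men in the two exercise arms as if the psychosexual component had not changed their uptake of treatment. Whatever benefit came through that uptake is credited to the covariate and not to the arm.

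There is a second problem. Aid use and later sexual health are likely to share causes, such as motivation or the severity of dysfunction. Conditioning on aid use then links allocation to those causes and can bias the arm coefficient. The result is not the total effect of being assigned to the combined intervention, and it is not a secure direct effect either. At stake is the test of whether the combination beats exercise alone.

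**Working it through.** **Inputs** (Statistical analysis section): SD of change about 22 points and exercise versus usual care difference about 11 points, both on the QLQ-PR25 sexual activity domain; psychosexual effect d = 0.5 from earlier psycho-educational trials, assumed additive to exercise; two-sided alpha 0.05; power 80%; 64 per group; attrition up to 20% in each period; 77 per group and 87% power at follow-up.

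**Step 1. The plan's own figures.** For exercise versus usual care, d = 11/22 = 0.5. For Exercise + Psychosexual versus Exercise, additivity gives d = 0.5 from the psychosexual trials. The two contrasts share a standardised size, but the 11 points belong to the first only.

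- Normal approximation: n = 2(1.960 + 0.842)²/0.5² = 62.8, so 63. The t-test gives 63.8, so 64, with power 80.1%.
- Attrition: 64/0.8 = 80 per arm, 240 in total.
- Follow-up: 240 × 0.8 × 0.8/2 = 76.8, so 77 per group. Power is 87.3% (normal) or 86.9% (t-test).

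All stated figures reproduce, and all assume that the full d = 0.5 is what the model estimates.

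**Step 2. Effect left after adjustment.** Let m be the share of the effect that runs through on-study aid use. The documents give no value, so m is an assumption. The adjusted contrast aims at d × (1 − m). Power is the probability that |T| exceeds its critical value, with 2n − 2 degrees of freedom and non-centrality d(1 − m)√(n/2). At n = 64 and m = 0 the non-centrality is 0.5 × √32 = 2.83.

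| Share m | Effect left, 0.5(1 − m) | Power, 64 per group | Power, 77 per group |
|---|---|---|---|
| 0 | 0.50 | 80% | 87% |
| 10% | 0.45 | 71% | 79% |
| 20% | 0.40 | 61% | 69% |
| 30% | 0.35 | 50% | 58% |
| 50% | 0.25 | 29% | 34% |

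**Step 3. Check with the covariate in the model.** Step 2 shrinks d at a fixed SD. It ignores the residual variance that a prognostic covariate removes and the precision lost because the covariate is correlated with arm. A simulation includes both: 64 per arm, total effect 0.5 SD, 4,000 runs per scenario, aid use 30% in the comparator. Uptake and aid effect are assumptions. The indirect effect is the difference in uptake times the aid effect; in the first row (0.50 − 0.30) × 0.5 = 0.10, which is 20% of 0.5.

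| Aid use, combined arm | Aid effect (SD) | Indirect effect | Adjusted estimate | Power, unadjusted | Power, adjusted |
|---|---|---|---|---|---|
| 50% | 0.5 | 0.10 | 0.40 | 80% | 61% |
| 60% | 0.5 | 0.15 | 0.35 | 81% | 50% |
| 60% | 0.8 | 0.24 | 0.26 | 80% | 32% |
| 70% | 0.8 | 0.32 | 0.18 | 80% | 17% |

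The first two rows (shares 20% and 30%) match Step 2, so the two omissions roughly cancel in these scenarios. The unadjusted estimate stays at about 0.50 throughout. The simulation has no causes shared by aid use and outcome, so it shows only the loss of the mediated part and not the additional bias.

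**The case against.** The best defence is that the adjustment sentence is a list of examples in the Randomisation section, not a model specification. The analysis section names no on-study covariate and no model as primary, so a detailed analysis plan might never use aid use in the main test. This is fair as far as it goes: that the primary contrast will be adjusted in this way is an inference. But aid use during the study is an explicit item under a firm statement that such factors will be adjusted for, and the analysis section does not limit covariates to baseline. Nothing in the article takes the commitment back.

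Several stronger readings are tempting and are not supported:

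- **Relationship satisfaction as a second mediator.** The timing bracket belongs to sexual aids only, and the hypotheses do not name relationship satisfaction as a route. It is a secondary endpoint ("The Dyadic Adjustment Scale will assess relationship satisfaction between participants and their partners"), but "All measurements for primary and secondary endpoints will take place at baseline, post-intervention and 1 year follow-up", so a baseline value exists and adjusting for that is harmless. The text is merely silent on which value is meant.
- **Side effects and co-morbidities as on-study covariates.** They too carry no timing.
- **Loss of the whole mechanism of hypothesis 2.** The session also covers stress management, coping and goal setting. Only the part carried by aid use is removed.
- **Damage to hypothesis 1.** The pathways listed for exercise do not include aid use, so the documents show no loss there.
- **Men without a partner dropping out of the model.** Nothing says so, and their handling is ordinary analysis-plan detail.

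It is also true that the power figures rest on an assumed share. They are a range and not an estimate.

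**Conclusion.** The concern holds for sexual-aid use during the study and for cancer treatment added during the study. Both are post-randomisation variables presented as potential confounders, which they cannot be. Aid use is in addition a mediator by the protocol's own hypothesis, so adjusting for it works against the Exercise + Psychosexual versus Exercise comparison. For added cancer treatment the documents name no such role; the objection is only that it arises after allocation.

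The loss of the mediated part is downward if, as the protocol theorises, the intervention raises aid use and aid use improves sexual health. With a mediated share between 10% and 50%, power at 64 per group would be between about 71% and 29% instead of 80%. The bias from shared causes has no direction or size that the documents allow one to work out, so the net error could differ from these figures. What does not depend on any assumed share is that the adjusted contrast is not the total effect that the intention-to-treat analysis should report.

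**What to change.** 1. State that covariates in all efficacy models are limited to values fixed before randomisation: baseline outcome score, the minimisation factors and, if wanted, pre-randomisation aid use and baseline relationship status and satisfaction.
2. In the adjustment list of the Randomisation section, delete the on-study element of the sexual-aid bracket and the item on cancer treatment added during the study.
3. State that relationship satisfaction, side effects and co-morbidities enter only as baseline values.
4. Report on-study aid use by arm as the secondary endpoint it already is. If its role in the effect is of interest, put it in a separate mediation analysis labelled exploratory, with its assumptions about shared causes stated.

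The cost is wording. No data, visits or participants change, and the stated sample size and power stay as they are. The change should be made before any analysis by arm.
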